### 12.6.2 Secondary endpoint analysis

Secondary efficacy variables are:

1. the treatment associated changes of oxygenation as measured by the  $\text{PaO}_2$  /  $\text{FiO}_2$  ratio until day 7 of therapy,
2. the ventilatory plateau pressure until day 7 of therapy,
3. the Murray lung injury score (a composite variable that includes components of oxygenation, compliance, positive end-expiratory pressure, and the appearance of the chest radiograph),
4. ventilation parameters: tidal volume ( $V_t$ ), positive endexpiratory pressure (PEEP), respiratory rate,  $\text{FiO}_2$ , PIP, mean airway pressure, peak airway pressure until day 7 of treatment
5. the duration of stay at ICU in the first 28 days,
6. the duration of controlled ventilation period until extubation,
7. the number of days free from ventilatory support [for > 48 h] in the first 28 days,
8. the survival status at day 28,
9. the local and systemic safety and tolerability and to identify possible dose related adverse events.

Secondary efficacy variables will be presented using appropriate descriptive methods, and will be analysed in an explorative sense: Mann-Whitney U-Test (Variable 1, 2, 3, 4), Kaplan-Meier estimates (variable 5, 6, 7, 8), and contingency tables (variable 9)

Statistical tests of the secondary efficacy variables and the p-values attached to them will be regarded as descriptive and not as tests of hypotheses.

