### **9.2 Randomization and stratification**

Subjects will be stratified regarding SOFA-Score (Sepsis-related Organ Failure Assessment) (Vincent, et al., 1996). Cut-off will be made at SOFA scores > 10. Therefore, there will be 2 subgroups (SOFA score ≤ 10, SOFA score ≥ 11). The GOCA score (Artigas, et al., 1998) will be assessed too, to be able to determine different causes of ALI.

Each subject will be randomised to one of 2 groups according to a randomization schedule prepared under the control of Bioconsult GmbH.

A stratified Randomization (strata: SOFA score ≤ 10, SOFA score ≥ 11) will be performed. Treatment allocation will be done using random permuted blocks within strata.

Randomization data will be kept strictly confidential, accessible only to authorised persons, until the time of unblinding. Authorised persons are:

- IT manager of Bioconsult GmbH,
- Drug packaging contractor.

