### 9.5.2 Screening investigation (Day 0)

Written informed consent must be obtained prior to embarking into any study related procedures. For patients that are temporarily unable to consent (e.g. comatose patients) a subsequent informed consent has to be provided.

The screening investigation aims to screen patients for potential participation. Inclusion and exclusion criteria will be checked.

Demographic data (age, ethnicity, height, weight and gender), vital signs (pulse rate, respiratory rate and temperature), the medical history (including the Glasgow Coma Scale) as well as concomitant medication will be documented. A blood sample for the evaluation of blood gases, clinical chemistry and hematology will be taken. The following scores will be obtained: GOCA (Artigas, et al., 1998), SOFA (Vincent, et al., 1996) and the lung injury score (Murray, Matthay, Luce, & Flick, 1988). The EVLW will be measured via PiCCO® technique. Hemodynamic parameters (HR, systolic BP, MAP, CI, PBV, 24 hours fluid balance and cardiac output) will be analyzed. For women with childbearing potential, a pregnancy test will be performed. Furthermore, the oxygenation index ( $\text{PaO}_2/\text{FiO}_2$ ), the ventilatory plateau pressure and ventilation parameters ( $V_t$ , PEEP, PIP, respiratory rate,  $\text{FiO}_2$ , mean airway pressure and peak airway pressure) will be obtained.

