### *Murray Lung Injury Score (Murray, Matthay, Luce, & Flick, 1988)*

The Murray Lung Injury Score is a composite variable that includes components of oxygenation, lung compliance, positive end-expiratory pressure and the appearance of the chest radiograph. It evaluates the extent of acute pulmonary damage. The Lung Injury Score will be assessed at screening as well as daily until end of treatment.

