### *Oxygenation index*

The oxygenation index will be assessed at screening and furthermore daily the changes of oxygenation index until end of treatment. It will be calculated from  $PaO_2$  and  $FiO_2$  as the  $PaO_2/FiO_2$  ratio (ratio of arterial oxygen tension to the fraction of inspired oxygen).

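### The plain Mann-Whitney test named for secondary variables 1 to 4 leaves collected Day 0 values and the SOFA stratum largely unused, at some cost in precision but none in validity

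*Protocol*

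**What the plan says.** Section 12.6.2 lists nine secondary variables and fixes the method for each: "Mann-Whitney U-Test (Variable 1, 2, 3, 4), Kaplan-Meier estimates (variable 5, 6, 7, 8), and contingency tables (variable 9". It names no covariate or stratum. It also says that the secondary tests and their p-values "will be regarded as descriptive and not as tests of hypotheses".

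The wording of the variables differs. Variable 1 is "the treatment associated changes of oxygenation as measured by the" PaO2/FiO2 ratio, which is a change. Variable 2 is "the ventilatory plateau pressure until day 7 of therapy", which is a level, and variables 3 and 4 are also worded as levels.

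All four have a Day 0 value:

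- Section 9.5.2 collects "the ventilatory plateau pressure and ventilation parameters" at screening.
- Section 9.5.6 says of the Murray score: "The Lung Injury Score will be assessed at screening as well as daily until end of treatment".
- Section 9.5.6 says of PaO2/FiO2: "The oxygenation index will be assessed at screening and furthermore daily the changes of oxygenation index until end of treatment".

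On allocation, section 9.2 states: "A stratified Randomization (strata: SOFA score ≤ 10, SOFA score ≥ 11) will be performed", using permuted blocks within the two strata. For the primary variable, section 12.6.1 allows ANCOVA or Mann-Whitney. Variables 1 to 4 are given Mann-Whitney only.

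**The concern.** In a 40-patient trial, the patient's own Day 0 value is usually the cheapest source of precision. With 20 per arm, the standard error of a baseline mean difference is sqrt(2/20) = 0.32 SD, so a chance imbalance above 0.3 SD arises in about one trial in three. At a baseline correlation of 0.5, an imbalance of 0.3 SD moves an unadjusted comparison of levels by 0.5 × 0.3 = 0.15 SD. Adjustment removes that component.

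Variables 1 to 4 are where the trial would show that a change in lung water reaches gas exchange and lung mechanics. Because their p-values are descriptive, the useful output is an estimated difference and its precision, and a Mann-Whitney p-value gives neither.

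This is not a detail left to the SAP. Section 12.4 has the SAP elaborate the analyses described in the protocol, and the protocol has already named the test. The point concerns values that are observed. Values missing after extubation or death are a separate matter.

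**Working it through.** **The plan's own figure.** The protocol states no effect size or power for the secondary variables. Its only calculation is for EVLW (section 12.2): a 40% difference with a 40% SD, so a standardised effect of 1.0, two-sided 5%, 80% power, 20 per group. Those inputs need 16 per group (normal approximation) or 17 (t-test), and 20 per group gives 87-89% power. The stated size is therefore conservative and does not bear on this point.

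**Inputs.** 20 per group and two-sided 5% are from section 12.2. The baseline-outcome correlation rho is not in the protocol; 0.3, 0.5 and 0.7 are assumed. Effects of 0.7 to 0.9 SD and normal data are also assumed.

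**Step 1: variance of the treatment difference, relative to the unadjusted level (= 1).** ANCOVA on Day 0: 1 − rho². Change score: 2(1 − rho).

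| rho | ANCOVA | Reduction | Change score | 40 adjusted patients equal |
|---|---|---|---|---|
| 0.3 | 0.91 | 9% | 1.40 | 40/0.91 = 44 |
| 0.5 | 0.75 | 25% | 1.00 | 40/0.75 = 53 |
| 0.7 | 0.51 | 51% | 0.60 | 40/0.51 = 78 |

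A change score therefore only matches the raw level at rho 0.5 and is worse below it. This is the relevant comparison for variable 1.

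**Step 2: power by formula.** Noncentral t with noncentrality d × sqrt(20/2). For Mann-Whitney, multiply by sqrt(0.955), its asymptotic efficiency under normality, with 38 df. For ANCOVA, divide by sqrt(1 − rho²), with 36 df. Example at d = 0.7: 0.7 × 3.162 = 2.214; Mann-Whitney 2.163; ANCOVA at rho 0.5, 2.214/0.866 = 2.556.

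| Effect | Mann-Whitney on level | ANCOVA, rho 0.3 | rho 0.5 | rho 0.7 |
|---|---|---|---|---|
| 0.7 SD | 55.9% | 61.7% | 70.1% | 85.5% |
| 0.8 SD | 67.3% | 73.3% | 81.1% | 93.1% |

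The gains in points are 5.8, 14.2 and 29.6 at 0.7 SD, and 6.0, 13.8 and 25.8 at 0.8 SD.

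**Step 3: power by simulation.** 20 per group, 4,000 runs per scenario, effect 0.91 SD (80% power for an unadjusted t-test). The two strata are equal in size, differ by 0.6 SD at baseline, and act on the outcome only through baseline.

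| Method | rho 0.3 | rho 0.5 | rho 0.7 |
|---|---|---|---|
| Mann-Whitney on level | 77% | 78% | 77% |
| Mann-Whitney on change | 62% | 78% | 94% |
| Stratified Wilcoxon, no baseline | 77% | 78% | 78% |
| Rank ANCOVA, baseline and stratum | 80% | 87% | 95% |
| ANCOVA, baseline and stratum | 82% | 89% | 97% |

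Simulation over 0.7 to 0.9 SD puts the gain of ANCOVA over Mann-Whitney on the level at about 4-6, 10-14 and 20-29 points. A further 8,000-run simulation at rho 0.3 gave, for 0.7/0.8/0.9 SD, Mann-Whitney 55.5/67.5/78.1% and rank ANCOVA 58.2/70.7/80.4%: gains of 2.7, 3.2 and 2.3 points.

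**Step 4: validity.** With no treatment effect, the plain Mann-Whitney test on the level rejected in 4.1-5.0% of runs. Nothing is inflated.

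**The case against.** The strongest case against has four parts.

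- **These analyses decide nothing.** Section 12.6.2 calls them exploratory, and no sample size, error rate or decision rests on them. This stands and keeps the point minor. It does not remove it, because a descriptive analysis is judged by how precisely it estimates.
- **The test is not wrong.** A Mann-Whitney p-value already allows for chance imbalance, and stratified allocation limits imbalance in severity. This also stands: the issue is efficiency alone.
- **A rank test suits some of these variables.** The Murray score is an ordinal composite, and PEEP, FiO2 and tidal volume are ventilator settings. This stands in part and is why a rank method should remain as a sensitivity analysis.
- **The size is assumed.** The protocol supplies no correlation, and the 1 SD effect in section 12.2 belongs to EVLW. This stands, so only a range can be given.

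A reader might also infer more than the protocol supports:

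- **That Day 0 is ignored throughout.** Variable 1 is a change. At rho 0.7, Mann-Whitney on change has 78/88/93% power for 0.7/0.8/0.9 SD against 80/90/95% for rank ANCOVA, so little is lost there.
- **That omitting the stratum is itself costly.** In the scenarios run, the stratified Wilcoxon test matched the plain one. A stratum with a strong direct effect on outcome was not examined.
- **That survival at Day 28 is tested without the stratum.** Section 12.6.2 names only Kaplan-Meier estimates for variable 8 and fixes no comparison test.
- **That a gain of at least 5 points is assured.** At rho 0.3 a rank ANCOVA gains 2-3.

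**Conclusion.** The point holds as a minor one about efficiency. Section 12.6.2 fixes a test that cannot use the SOFA stratum for variables 1 to 4, or the Day 0 value for variables 2 to 4, and uses Day 0 for variable 1 only through a change score.

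Nearly all of the loss comes from baseline rather than from the stratum. Its size rests on an assumed correlation, approximate normality and effects of 0.7 to 0.9 SD. It is small at a correlation of 0.3 and substantial at 0.7. For variable 1 the loss is largest at low correlations, where subtraction adds noise, and small at high ones. Validity, the primary analysis and the sample size are untouched.

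**What to change.** In section 12.6.2, replace the Mann-Whitney test for variables 1 to 4 by ANCOVA on the measured scale. Take the on-treatment value (the day or summary that the SAP specifies) as outcome, with its Day 0 value and the SOFA stratum (≤ 10, ≥ 11) as covariates. Report the adjusted difference with its 95% CI as an exploratory estimate. Keep the Mann-Whitney test as a sensitivity analysis, or a rank ANCOVA for clearly non-normal variables. A rank ANCOVA gives its difference in rank units, so it should not be the source of the reported estimate.

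The cost is a wording change in the protocol and the SAP, two degrees of freedom per model (36 instead of 38 with 40 patients) and a distributional assumption. No new data or patients are needed. No change is proposed for variable 8.

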## 6. BACKGROUND INFORMATION

### 6.1 Background

The pulmonary permeability oedema is characterized by a reduced alveolar liquid clearance capacity, combined with an endothelial/epithelial hyper-permeability. Two separate barriers form the alveolar–capillary barrier: (a) the microvascular endothelium and (b) the alveolar epithelium. Both endothelial and epithelial injury and increased vascular permeability lead to the formation of the pulmonary permeability oedema in the life-threatening condition Acute Lung Injury. There are many possible causes of ALI, such as inhaling high concentrations of smoke, toxins, or oxygen; severe burns; blood infections; lung infections; or trauma to other parts of the body.

Acute Lung Injury is a condition in which the capacity of the lungs to oxygenate the blood is greatly reduced, even if oxygen is administered in high concentrations. The lungs are composed of tiny structures called alveoli. It is in the alveoli where oxygen and carbon dioxide are exchanged between the air that is inhaled and the blood that perfuses the lungs in tiny vessels called capillaries. When the lungs are injured and / or the surrounding capillaries are injured, blood and fluids begin to leak from the capillaries, into the alveoli. Subsequently, air cannot enter the alveoli and pass into the blood, which means that the normal functions of the lung tissue are impaired. This will lead to inflammation (a response to the injury caused to the tissue that includes swelling) and progressive formation of scar tissue in the walls of the alveoli. Without treatment, the gas exchange derangement and abnormal lung mechanics can result in progressive hypoxemia, respiratory muscle fatigue, and eventual respiratory arrest and death.

For Acute Lung Injury and the Acute Respiratory Distress Syndrome mortality rates of 30% to 60% have been reported (Review in: (Ware & Matthay, 2000)).

In patients with ALI there exists a close correlation between mortality and the capacity of the patients to resolve the pulmonary oedema. Maximal alveolar fluid clearance is associated with better clinical outcomes (Ware & Matthay, 2001).

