#### **9.5.4 End-of-study (EOS) interview (Day 28 + 7 days)**

On day 28 (+ 7) a follow-up/ EOS interview will take place via telephone. Survival will be documented. Adverse events and concomitant medication will be documented and the ventilation-free days (for > 48h) until day 28 will be listed. Furthermore, the duration of stay at ICU in the first 28 days and the duration of controlled ventilation period until extubation will be recorded.

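### Section 12.6.2 prescribes Kaplan-Meier for ventilator-free days, which are a count, and for ICU stay and ventilation duration, where death competes, with no rule for deaths

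*Protocol*

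**What the plan says.** Section 12.6.2 of the protocol numbers nine secondary variables and gives each a method. Variables 1 to 4 get the Mann-Whitney test. For the rest it prescribes "Kaplan-Meier estimates (variable 5, 6, 7, 8), and contingency tables (variable 9". The four variables assigned to Kaplan-Meier are:

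- 5: "the duration of stay at ICU in the first 28 days"
- 6: "the duration of controlled ventilation period until extubation", with no time window stated
- 7: "the number of days free from ventilatory support [for > 48 h] in the first 28 days"
- 8: "the survival status at day 28"

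The same section says that the secondary tests and p-values "will be regarded as descriptive and not as tests of hypotheses". Section 9.5.4 has these outcomes recorded at the telephone interview on day 28 (+7), where survival is documented and "the ventilation-free days (for > 48h) until day 28 will be listed".

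On how often patients die, section 6.1 notes that for acute lung injury and ARDS "mortality rates of 30% to 60% have been reported", without a time horizon. The synopsis and sections 7.2, 9.5.4 and 12.6.2 do not say how a death enters variables 5, 6 or 7. The only missing-data rule, last observation carried forward in sections 8.1.6 and 12.5, covers the primary variable alone.

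**The concern.** One method is assigned to four variables of different kinds.

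**Variable 7** is a number of days out of 28, and a high value is good. If every patient has a complete count, Kaplan-Meier only redraws the distribution of the counts. If deaths are censored, a patient who dies on the ventilator with no free days leaves the risk set at zero instead of counting as the worst result.

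**Variables 5 and 6** end in discharge or extubation, or in death. The two usual ways of putting such data into Kaplan-Meier both go wrong:

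- Censoring at death treats the dead as if they would later have been extubated or discharged at the same rate as the survivors.
- Letting death end the duration scores an early death as a short stay.

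These are the patient-relevant outcomes of a proof-of-concept trial and will help to decide whether development continues. If mortality differed between the arms, the first coding would hide the difference on these curves. The second would turn it round.

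**Working it through.** The protocol gives no expected figure for variables 5 to 7, so there is none to reproduce. The check asks how far each coding of death moves the result, taking ventilation until extubation as the example.

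**Inputs**

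- Window: 28 days (sections 9.5.4 and 12.6.2).
- Deaths before extubation: 30% and 60%, the literature range in section 6.1, used here as a 28-day proportion by assumption; 10% is added as a low case.
- Median time to extubation in the absence of death: 7, 10 or 14 days. This is an assumption; the protocol gives no extubation rate.
- Constant hazards: a for extubation, b for death before extubation. Follow-up to day 28 is complete.

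**Formulas**

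- a = ln 2 / median.
- Kaplan-Meier extubation probability at day 28, deaths censored: 1 - exp(-28a).
- True proportion extubated alive (cumulative incidence): a/(a+b) × [1 - exp(-28(a+b))].
- b is solved so that b/(a+b) × [1 - exp(-28(a+b))] equals the assumed proportion of deaths.

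**One case in full** (median 10 days, 30% deaths)

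- a = 0.693/10 = 0.0693 per day.
- Kaplan-Meier: 1 - exp(-1.941) = 0.856.
- Solving gives b = 0.0324, so a+b = 0.1017.
- Cumulative incidence: 0.0693/0.1017 × [1 - exp(-2.848)] = 0.681 × 0.942 = 0.642.
- Overstatement: 0.856 - 0.642 = 0.214, or 21 points.

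**All cases** (excess computed before rounding)

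| Median (days) | Deaths | Kaplan-Meier, deaths censored | Cumulative incidence | Excess |
|---|---|---|---|---|
| 7 | 10% | 0.938 | 0.855 | 0.083 |
| 7 | 30% | 0.938 | 0.682 | 0.256 |
| 7 | 60% | 0.938 | 0.399 | 0.538 |
| 10 | 10% | 0.856 | 0.788 | 0.069 |
| 10 | 30% | 0.856 | 0.642 | 0.214 |
| 10 | 60% | 0.856 | 0.393 | 0.464 |
| 14 | 10% | 0.750 | 0.695 | 0.055 |
| 14 | 30% | 0.750 | 0.578 | 0.172 |
| 14 | 60% | 0.750 | 0.373 | 0.377 |

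The excess is 6 to 8 points at 10% deaths, 17 to 26 at 30% and 38 to 54 at 60%.

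**Sensitivity to the assumption.** Suppose instead that death and extubation together always reach 90% by day 28. The total 28-day hazard is then -ln(0.1) = 2.303. With 30% dead and 60% extubated, the extubation share is 2.303 × 60/90 = 1.535, and Kaplan-Meier gives 1 - exp(-1.535) = 78% against a true 60%. With 40% dead and 50% extubated it gives 72% against 50%; with 60% and 30%, 54% against 30%. The excess is then 18 to 24 points. Its size depends on the assumptions; its direction does not.

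**Two arms with the same extubation hazard** (median 10 days), 30% deaths in one and 60% in the other:

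| Handling of death | 30% deaths | 60% deaths | Reading |
|---|---|---|---|
| Censored: Kaplan-Meier extubation probability | 0.856 | 0.856 | excess deaths invisible |
| Ends the duration: median ln 2/(a+b) | 6.8 days | 4.0 days | arm with more deaths looks better |
| Kept at risk to day 28: Kaplan-Meier (simulated, 400,000 patients) | 0.642 | 0.391 | agrees with cumulative incidence, 0.642 and 0.393 |
| Ventilator-free days, death = 0: mean (simulated) | 12.8 | 8.8 | excess deaths visible |

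**The case against.** The strongest reply is that Kaplan-Meier need not fail for variables 5 and 6. If patients who die are kept at risk to day 28 as never extubated or discharged, and follow-up is otherwise complete, the curve equals the cumulative incidence, as the third row of the last table shows. The protocol adopts neither harmful coding; it states none. Sections 12 and 12.4 leave further detail to a SAP finalised before unblinding, and a censoring rule can properly go there. This stands. A reader might infer that the estimates for variables 5 and 6 are bound to be wrong; the document does not support that.

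A reader might also infer that the trial would pass off harm as benefit. That goes too far as well. Hiding a mortality difference and reversing it belong to two different codings that cannot both apply. Survival at day 28 is variable 8 in the same list and would be reported alongside. The secondary p-values are declared descriptive, and the primary analysis of extravascular lung water does not use these curves.

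The mortality figure is open to challenge too. It comes from the literature, includes ARDS and has no time horizon, while section 8.1.3 excludes septic shock. The trial's own rate may differ.

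Two things survive the reply. The method itself is fixed in the protocol, and for variable 7 no death rule makes a count into a time to an event. For variables 5 and 6, naming Kaplan-Meier beside survival with no death rule invites one of the two misleading codings.

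**Conclusion.** The point holds as a moderate one. Kaplan-Meier does not suit variable 7. For variables 5 and 6 it is safe only under a handling of death that the protocol does not state.

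If deaths are censored, extubation by day 28 is overstated by about 17 to 26 points at 30% deaths before extubation, and by 6 to 8 points even at 10%. If death ends the duration, the arm with more deaths shows the shorter median (4.0 against 6.8 days in the example). These sizes rest on constant hazards, a median time to extubation without death of 7 to 14 days (10 in the two-arm example) and complete follow-up. None of these comes from the protocol.

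The reach is limited to explorative secondary endpoints. Kaplan-Meier for survival is appropriate, and the primary conclusion is unaffected.

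**What to change.** In section 12.6.2:

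- Keep Kaplan-Meier for variable 8 only.
- For variables 5 and 6, report by arm the cumulative incidence to day 28 of discharge from ICU alive and of extubation alive, with death as a competing event. Keeping deaths at risk to day 28 is equivalent when follow-up is complete.
- Analyse variable 7 as a count, with 0 days for any patient who dies by day 28, by the Mann-Whitney test already named for variables 1 to 4. Deaths will tie at 0, so use the tie-corrected form.

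The cost is a few lines of text and a little programming. One thing needs confirming: Table 1 and section 9.5.4 list durations, days until extubation and survival, but do not explicitly list the times of extubation, ICU discharge and death. The time of death is needed in any case for the survival curve.
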